**Methods:**

The Joint PRehabilitation with Exercise and Protein (Joint PREP) study is a feasibility study for a multicentre, two-arm, parallel group, pragmatic, RCT to evaluate the clinical and cost-effectiveness of prehabilitation for frail patients undergoing total hip or knee replacement. Sixty people who are ≥ 65 years of age, frail according to the self-reported Groningen Frailty Indicator, and scheduled to undergo total hip or knee replacement at 2–3 hospitals in England and Wales will be recruited and randomly allocated on a 1:1 ratio to the intervention or usual care group. The usual care group will receive the standard care at their hospital. The intervention group will be given a daily protein supplement and will be asked to follow a home-based, tailored daily exercise programme for 12 weeks before their operation, in addition to usual care. Participants will be supported through six follow-up calls from a physiotherapist during the 12-week intervention period. Study questionnaires will be administered at baseline and 12 weeks after randomisation. Embedded qualitative research with patients will explore their experiences of participating, reasons for nonparticipation, and/or reasons for withdrawal or treatment discontinuation. Primary feasibility outcomes will be eligibility and recruitment rates, adherence to the intervention, and acceptability of the trial and the intervention.

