### Outcome assessment and progression criteria

#### Primary feasibility outcomes

The primary outcome is to determine the feasibility of a definitive RCT. This will involve evaluation of the key parameters of uncertainty for a RCT which are eligibility and recruitment rates, adherence to the intervention, and acceptability of the trial and the intervention. Eligibility and recruitment will be assessed by collecting detailed screening and recruitment records to allow review of the number of eligible, approached, and consented patients, alongside information on reasons for non-eligibility and nonparticipation. To assess adherence to the intervention, participants will be provided with a log form and asked to keep a daily record of whether they eat their protein and complete their exercises. Further details about reasons for non-adherence will be recorded on a proforma during the intervention telephone calls. Participants will be considered to have adhered to the intervention if they consumed the protein on at least 4 days per week for at least 10 weeks and/or completed the exercises at least 3 days per week for at least 10 weeks (or 80% of intervention duration if the time available for the intervention is shorter than 12 weeks, e.g. if the participant is offered an operation date earlier than expected). Acceptability of the trial and intervention will be evaluated through qualitative interviews, questions in the study questionnaires, retention rates, and reasons for withdrawal.

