#### Progression criteria for a full-scale RCT

The key feasibility issues will be considered on a red (stop), amber (amend), and green (proceed) traffic light system. The feasibility of a full trial will be determined by overall recruitment, retention, and adherence rates. Recruitment will be considered achievable if the rate observed is > 23% (lower limit of the 95% confidence interval for a 30% recruitment rate based on 200 screened). Similar criteria will be applied for retention: i.e. > 70%, for an 80% retention rate based on 60 participants, for adherence: > 37%, and for a 50% adherence rate based on 60 participants. If all three elements fail to reach the threshold (i.e. recruitment is ≤ 23%, retention is ≤ 69%, and adherence is ≤ 37%), a RCT will not be considered feasible. If one or two elements fail to reach the threshold, we will consider how the trial can be modified to address the shortfall. Examples may include modifying recruitment processes or study documents (recruitment), providing additional support/advice (retention and adherence), or offering alternative protein-rich products/exercises (retention and adherence). If all three elements are above the threshold, the trial will be considered feasible.

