### Sample size

As this is a feasibility study, we have based our sample size on recruitment rate. If we identify 200 eligible patients, we can estimate a recruitment rate of 30% (i.e. 60 participants) to within a 95% confidence interval of ± 6.35%.

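### The 37% adherence bar is derived from 60 participants, but only the roughly 30 allocated to the intervention can adhere, so its confidence-limit basis and implied precision do not hold

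*Protocol article*

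**What the plan says.** Under Progression criteria for a full-scale RCT, the recruitment bar of 23% is explained as the "lower limit of the 95% confidence interval for a 30% recruitment rate based on 200 screened". The next sentence begins "Similar criteria will be applied for retention" and carries the same approach to retention (bar 70%, target 80%, 60 participants) and to adherence (bar 37%), the latter "for a 50% adherence rate based on 60 participants". All three above their bars means the trial is feasible. One or two below leads to modification. Only a miss on all three makes the RCT not feasible, and the adherence part of that condition is given in "retention is ≤ 69%, and adherence is ≤ 37"%.

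The figure of 60 is the total sample: under Sample size, "we can estimate a recruitment rate of 30% (i.e. 60 participants"). The abstract's Methods paragraph says that these people are "randomly allocated on a 1:1 ratio to the intervention or usual care group". The Intervention section assigns the programme to the intervention arm, and Usual care says that the other arm gets no advice or treatment beyond routine care. Under Primary feasibility outcomes, adherence is judged from a log in which people are "asked to keep a daily record of whether they eat their protein and complete their exercises", with minimum days per week over at least 10 weeks.

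**The concern.** Adherence to the supplied protein and the prescribed exercises has no meaning in the usual care arm, and the article defines none for it. The number of people on whom adherence can be observed is therefore about half of 60. A base of 60 suits retention, which concerns both arms, and may have been carried over from there.

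Adherence is a primary feasibility outcome and one of the three elements behind the progression decision. If the bar is presented as a lower confidence limit, readers will take it that an observed rate at or below 37% would be unusual when true adherence is 50%. That depends directly on the number of people observed. With half the number, the interval is wider by a factor of √2 and the bar no longer sits at the limit that it is said to be.

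**Working it through.** **Inputs.** Total randomised 60 (Sample size). Allocation 1:1 (abstract, Methods), so about 30 per arm. Target adherence 50%, bar >37%, stated basis 60 (Progression criteria). Recruitment target 30% on 200, with precision given under Sample size as "to within a 95% confidence interval of ± 6.35"%.

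**Step 1: identify the plan's method.** The simple (Wald) limit is p − 1.96 × √(p(1 − p)/n).
- Recruitment: 1.96 × √(0.30 × 0.70/200) = 6.35 points, as stated. Lower limit 23.65% (bar 23%).
- Retention: 1.96 × √(0.80 × 0.20/60) = 10.12 points. Lower limit 69.88% (bar 70%, with 69% in the stop condition).
- Adherence as stated: 1.96 × √(0.50 × 0.50/60) = 12.65 points. Lower limit 37.35% (bar 37%).

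So the plan's 37% is reproduced, but with both arms in the denominator.

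**Step 2: same rule, intervention arm only.** 1.96 × √(0.50 × 0.50/30) = 17.89 points. The interval is 32.1% to 67.9%.

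The choice of interval does not rescue 37%. The lower limit with n = 30 is 33.2% by Wilson or Agresti-Coull, 32.8% by Jeffreys, 31.3% by Clopper-Pearson and 30.4% by Wald with continuity correction.

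**Step 3: chance of missing the bar when true adherence is 50% (binomial).**

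| Basis | Needed to pass | P(miss) |
|---|---|---|
| n = 60, >37% | 23 or more | P(X ≤ 22) = 2.6% |
| n = 30, >37% | 12 or more | P(X ≤ 11) = 10.0% |
| n = 30, >32% | 10 or more | P(X ≤ 9) = 2.1% |

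**Step 4: effect on the overall decision.** Take all three true rates at their targets and treat the elements as independent. Recruitment passes with probability 1 − P(X ≤ 46 of 200) = 0.983, and retention with 1 − P(X ≤ 42 of 60) = 0.957.
- All three pass, adherence on n = 60: 0.983 × 0.957 × 0.974 = about 92%.
- All three pass, adherence on n = 30: 0.983 × 0.957 × 0.900 = about 85%.
- All three miss: 0.017 × 0.043 × 0.026 = about 0.002% on n = 60, and 0.017 × 0.043 × 0.100 = about 0.007% on n = 30.

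**Step 5: the other side of lowering the bar (n = 30).** At a true adherence of 30%, P(pass) is 16% with >37% and 41% with >32%. At a true 35% it is 35% and 64%.

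**Step 6: sensitivity to arm size.** Stratified allocation need not give exactly 30. For 28 to 32 people the lower limit runs from 31.5% to 32.7%, and the chance of missing >37% at a true 50% from 5.5% to 10.0%. It stays above 2.6% throughout.

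**The case against.** The strongest defence is that 37% still works as a decision rule. It can be applied to 30 people (12 or more adherers), it errs towards caution, and a team may choose a minimum without deriving it from an interval. That stands, and it means that the error lies in the stated justification and precision. A reader might infer that the bar itself is invalid and must come down. The article does not support that, and Step 5 shows that lowering it has a price.

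A reader might also infer that the error could wrongly stop the programme. It could not do so alone: a miss on adherence only leads to modification, and at target rates the chance of all three missing is negligible on either basis.

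Nor can the 10% be called four times an intended error rate. The article states no intended rate, and its own bars do not share one: at target, recruitment misses about 1.7% of the time and retention about 4.3%. The 2.6% is only what the stated basis implies.

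Read literally, a denominator of 60 would require 23 adherers from about 30 people (77% of the arm), and the 50% target would need every one of them to adhere. Nothing suggests that this is meant.

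Finally, the Statistical analysis section promises adherence with a 95% confidence interval, so the real uncertainty should be visible at reporting. The sample size rests on recruitment and is unaffected. Both points are fair, but neither corrects the basis given for the bar. The handling of unreturned logs is commonly left to the full protocol or analysis plan and is no part of this point.

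**Conclusion.** The point holds in a bounded form. The stated basis for the adherence bar is wrong: about 30 people can adhere, not 60, and no section of the article supports 60. By the plan's own method the half-width is about 17.9 points instead of 12.65, and the lower limit about 32% instead of 37%.

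The practical effect is a lower chance of a green result when the rates are in fact on target: about 85% rather than 92%. The shift is from green to amber; the stop decision is practically unchanged. These figures assume 60 randomised, an even split, true rates at target, and independence of the three elements.

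**What to change.** In Progression criteria for a full-scale RCT, change the basis for adherence from 60 to the roughly 30 participants allocated to the intervention, and state the precision as about ±18 points. Then choose one of two courses and say which:

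1. **Keep >37%** (12 or more of 30) as a chosen minimum. Remove the confidence-limit justification for adherence, and state that a true 50% would miss the bar about 10% of the time.
2. **Recompute the bar as >32%** (10 or more of 30) by the same rule. This brings the miss chance at a true 50% to 2.1%. Disclose that poor adherence then passes more easily: about 41% against 16% at a true 30%.

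Either course takes a sentence or two and changes nothing in study conduct or sample size. The cost is a less favourable stated precision and, under the second course, a weaker screen against poor adherence. The choice should be fixed before adherence results are judged against the bar.

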### Safety

Data on adverse events and serious adverse events will be collected and monitored by the research team to ensure the ongoing safety of participants. All serious adverse events during the intervention period will be notified and reviewed by the study sponsor (North Bristol NHS Trust).

### Withdrawal

Participants may choose to withdraw from the study at any time. Participants who withdraw will be invited to provide their reasons if they wish to do so, and these will be recorded on a proforma to allow identification of barriers to participating and highlight measures to facilitate continued participation in a future RCT.

### Embedded qualitative study

#### Patient interviews

Patients who are approached for the study will be invited to take part in a semi-structured face-to-face/telephone/online interview (according to preference) with a trained qualitative researcher. Interviews with patients who agree to be randomised in the feasibility study will explore their experiences of participating. For those who decline to be randomised or withdraw, interviews will explore reasons for nonparticipation and/or reasons for withdrawal or treatment discontinuation. Target numbers are around 15 to 20 patients who agree to be randomised, and 10 to 15 patients who decline to be randomised and/or are randomised but subsequently withdraw/discontinue treatment, with precise numbers of interviews being determined by principles of data saturation. Interviews will follow a topic guide, which covers experiences of randomisation, tolerability of the intervention, experience of participation, and data collection methods and any barriers or enabling factors that participants experienced in adhering to the intervention. For patients who decline to participate in the feasibility study, the questions will focus on reasons for declining or withdrawing and any barriers to participation.

#### Local research delivery team discussion groups

Group discussions with members of the local research delivery team from each site will be held to elicit their acceptability of the study design, their preference, and margins of equipoise and to understand any potential organisational barriers to RCT implementation and potential mitigation strategies. These will take place once the site has been open to recruitment for approximately 3–6 months to allow for reflection on the experiences of undertaking the study. The discussion groups will take place in person, at local sites, or online (guided by the preferences of the participants) and will be facilitated by the qualitative team. The group discussions will be recorded for the purposes of minute taking only, and the recording will then be deleted once the minutes have been written up. We will not seek consent as the purpose of the discussion is to inform the design of a future RCT rather than generate research data.

### Sample size

As this is a feasibility study, we have based our sample size on recruitment rate. If we identify 200 eligible patients, we can estimate a recruitment rate of 30% (i.e. 60 participants) to within a 95% confidence interval of ± 6.35%.

### Data management

Study data will be stored in the REDCap secure online data capture system. Data validation will be completed in REDCap and any data queries resolved with the site trial team. Participants’ personal data will be stored securely and will only be accessible to trial staff and authorised personnel. All study documents will be made available on request for monitoring and audit by the sponsor or the research ethics committee.

### Statistical analysis

This study is not powered to look at differences in outcomes between the intervention and usual care group. Data on recruitment, retention, and adherence will be reported using frequencies and proportions with 95% confidence intervals. Sample characteristics and outcome data will be summarised by means and standard deviations, medians and interquartile ranges, or frequencies and proportions as appropriate. Preoperative WOMAC scores will be summarised by group and compared descriptively to estimate the efficacy potential of the intervention.

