### Randomisation

Participants will be randomised by a member of the local research team using a computer-based tool (REDCap), stratified by study site and operation type (THR/TKR), with full allocation concealment. Randomisation will be conducted as soon as possible after the research team receive a completed baseline questionnaire. Participants will be informed of their treatment allocation by letter, followed by a telephone call for participants randomised to the intervention group to discuss arrangements for the intervention. Blinding of study participants will not be possible due to the nature of this intervention. After participants have been randomised, a letter will be sent to their GP to inform them of their participation in the Joint PREP study and their treatment allocation.

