### Questionnaires and data collection

All participants will be asked to complete questionnaires at baseline (after recruitment and prior to randomisation) and 12 weeks after randomisation. Questionnaires will be administered on paper or online, depending on participant preference. Nonresponders will be followed up with a reminder questionnaire and then a telephone call from the local research team to offer the option of completing the outcome measures over the telephone.

A schedule of assessment is provided in Table 1. Pain and function will be assessed using the Western Ontario and McMaster Universities Osteoarthritis Index (WOMAC) [26]. Health-related quality of life will be measured using the EQ-5D-5L [27] and capabilities with the ICECAP-O [28]. Other measures include the Groningen Frailty Indicator, Clinical Frailty Scale, Global Physical Activity Questionnaire [29], Exercise Self-Efficacy and Beliefs Questionnaire [30], and Protein Screener 55 + [31]. Participants will be asked to self-report their height and weight to allow BMI to be calculated. Participants in the usual care group will be asked about any changes to usual diet or usual exercise/physical activity in the past 12 weeks and, if so, what these changes were. Participants in the intervention group will be asked questions on the acceptability of the intervention.

The Clinical Frailty Scale will be completed by a healthcare professional when the patient attends the hospital for their routine preoperative assessment appointment so that self-reported and clinician-assessed versions of the Clinical Frailty Scale can be compared. Data will be extracted from participants’ medical records on preoperative comorbidities, indication for surgery, surgery details, length of hospital stay, discharge destination, preadmission residence, post-operative mobilisation, and post-operative complications up to 30 days after surgery (if surgery takes place within the study timeframe).

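### Efficacy potential is to be estimated from 12-week WOMAC by descriptive comparison alone, with no interval and no stated use of baseline WOMAC, so the estimate is noisier than it need be

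*Protocol article*

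**What the plan says.** The protocol article's Aims and objectives section includes efficacy potential among the quantities to be estimated. Secondary feasibility outcomes names the measure: the preoperative WOMAC score 12 weeks after randomisation. Statistical analysis gives the method: "Preoperative WOMAC scores will be summarised by group and compared descriptively to estimate the efficacy potential of the intervention". That section opens by saying that the study has no power for differences between groups. It promises 95% confidence intervals for recruitment, retention and adherence; for outcome data it promises summary statistics.

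On baseline data, Questionnaires and data collection says: "All participants will be asked to complete questionnaires at baseline (after recruitment and prior to randomisation) and 12 weeks after randomisation". WOMAC is the first instrument listed there. The schedule by instrument is in Table 1, which is not shown, so collection of WOMAC at baseline is a strong inference rather than a statement in the text.

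Randomisation is "stratified by study site and operation type (THR/TKR"). WOMAC is not a stratification factor.

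**The concern.** The aim is worded as estimation, but the stated method yields two sets of summaries side by side. No estimate of the difference with its uncertainty is specified, and neither section that describes the efficacy-potential outcome mentions baseline score, change or adjustment.

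Pain and function before randomisation can be expected to correlate with the same score 12 weeks later. With about 30 people per arm and no stratification on WOMAC, the groups may differ noticeably at baseline by chance, and part of that difference passes into the 12-week comparison. At stake is how well one named objective is met: a modest apparent benefit could be produced or masked by imbalance that a baseline-adjusted analysis would largely remove.

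**Working it through.** **Inputs from the article**
- 60 participants, who "will be recruited and randomly allocated on a 1:1 ratio to the intervention or usual care group": about 30 per arm.
- The progression threshold for retention is set "for an 80% retention rate based on 60 participants". 0.80 × 60 = 48, or 24 per arm if losses are equal.
- "As this is a feasibility study, we have based our sample size on recruitment rate". WOMAC did not enter the sample size, and the article gives neither its SD nor its correlation over 12 weeks.

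**Assumptions.** Results are in SD units, with a baseline-to-12-week correlation r of 0.5 to 0.7.

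**The plan's own figure.** Sample size says "we can estimate a recruitment rate of 30% (i.e. 60 participants) to within a 95% confidence interval of" ±6.35%. 1.96 × √(0.30 × 0.70 / 200) = 0.0635, so it is reproduced. It concerns recruitment only.

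**Chance baseline difference.** The SD of the difference in means is √(2/n per arm).
- 30 per arm: √(2/30) = 0.258.
- 24 per arm: √(2/24) = 0.289.

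The probability of an imbalance above 0.3 SD in either direction is 25% with 30 per arm and 30% with 24.

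**Carry-over into the raw 12-week difference.** A one-standard-error imbalance shifts it by r × SE.
- 30 per arm: 0.5 × 0.258 = 0.13; 0.7 × 0.258 = 0.18.
- 24 per arm: 0.5 × 0.289 = 0.14; 0.7 × 0.289 = 0.20.

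**Gain from baseline adjustment.** The standard error is multiplied by √(1 − r²).
- r = 0.5: √0.75 = 0.866, a 13% reduction.
- r = 0.7: √0.51 = 0.714, a 29% reduction.

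| 95% half-width (SD units) | 30 per arm | 24 per arm |
|---|---|---|
| Unadjusted, 1.96 × √(2/n) | 0.51 | 0.57 |
| Adjusted, r = 0.5 | 0.44 | 0.49 |
| Adjusted, r = 0.7 | 0.36 | 0.40 |

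Simulation of 10,000 trials with 30 per arm gave standard errors of 0.259 unadjusted, and 0.226 (r = 0.5) and 0.187 (r = 0.7) adjusted. The formula gives 0.258, 0.224 and 0.184, so it is slightly optimistic at this size.

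**What this means for the apparent signal, 30 per arm**
- No true effect: an observed difference of at least 0.3 SD arises in 25% of trials unadjusted, against 18% (r = 0.5) or 10% (r = 0.7) adjusted.
- Assumed true effect of 0.3 SD: the estimate has the wrong sign in 12% unadjusted, against 9% or 5% adjusted.

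**The case against.** The strongest reply is that a descriptive comparison is an accepted and cautious choice for a feasibility study that openly disclaims power, and that covariate adjustment is often left to an analysis plan, which is not shown here. Part of this stands. Silence on adjustment is not an error in itself, and a lack of power is a good reason to avoid a hypothesis test. It is not a reason to omit an interval, and the article does specify how efficacy potential will be assessed, so the point concerns stated text.

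A second reply is that readers could work out an unadjusted interval from reported means, SDs and group sizes. That is true if means and SDs are what is reported, but the baseline-adjusted estimate could not be recovered that way.

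A third is that adjustment leaves the interval wide. That also stands: the sample size is the main limit, and adjustment removes only the avoidable part.

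Three stronger readings are tempting, and the article does not support them:
- *Baseline WOMAC is discarded.* The text never says so. It is silent on its use, promises summaries of sample characteristics and outcome data, and its plural reference to preoperative scores could include baseline.
- *A misleading WOMAC difference could decide whether the full trial goes ahead.* Progression criteria for a full-scale RCT rests on recruitment, retention and adherence alone, and the section on patient and public involvement ties the grant application to feasibility.
- *Preoperative WOMAC is treated as a surrogate for the post-operative outcome.* Secondary feasibility outcomes says that the future primary outcome would be post-operative and offers the preoperative score only as an indication.

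**Conclusion.** The point holds as a recommendation. An objective to estimate efficacy potential is paired with a method that states no interval and no use of a baseline measure that is apparently to hand. The loss is moderate: a standard error larger than necessary by the margin that a 13% to 29% reduction would recover.

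This rests on the assumed correlation, on equal arms with equal losses, and on WOMAC being in the baseline questionnaire. At a correlation of 0.3 the reduction would be only about 5% (√(1 − 0.09) = 0.954); at 0.8 it would be 40%. The gain is credited to baseline WOMAC alone, because nothing in the article shows that site or operation type is strongly prognostic. The consequence is confined to how precisely, and how transparently, one secondary feasibility outcome is reported.

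**What to change.** In Statistical analysis, keep the by-group summaries and add one sentence: the between-group difference in 12-week WOMAC will be reported with a 95% confidence interval from a linear model adjusted for baseline WOMAC, study site and operation type, with no hypothesis test. Site and operation type belong in the model because randomisation is stratified on them.

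The model is affordable at this size. With three sites it has six coefficients (intercept, group, baseline, operation type, two for site), which leaves 48 − 6 = 42 residual degrees of freedom at 80% retention.

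The cost is a sentence of text. No new data are needed, provided that Table 1 confirms WOMAC at baseline; that should be checked first. If an unshown analysis plan already specifies this model, the article need only be brought into line with it.
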